### Mechanism exploration

2.16

#### Fecal collection and 16S ribosomal RNA sequencing analysis

2.16.1

After enrollment, participants will be required to maintain a stable diet, which will be documented through a food and medication diary. During stool sample collection, bowel frequency, consistency according to the Bristol stool scale (Lewis and Heaton, 1997), and any recent changes in dietary habits will be simultaneously recorded.

Fresh fecal samples will be collected prior to inclusion and 4 weeks post-treatment. Using disposable gloves, a spoon will mix the fecal samples to ensure that they are approximately the size of a broad bean before being placed in a fecal collection box. After collection, the samples will be immediately checked and stored at −80°C. Microbial DNA will be extracted from the fecal samples using a DNA extraction kit (MagPure Stool DNA KF Kit B; MAGEN, Guangzhou, China). The extracted DNA will be amplified via polymerase chain reaction targeting the highly variable V3-V4 regions of the 16S ribosomal RNA gene. The forward primer (338F 5’-ACTCCTACGGGAGGCAGCAG-3′) and reverse primer (806R 5’-GGACTACHVGGGTWTCTAAT-3′) will be utilized to amplify the V3-V4 region of the bacterial 16S ribosomal RNA gene. The libraries will be sequenced using the Illumina MiSe platform (Beijing Genomics Institution, Shenzhen, China).

Following the filtering of the raw data, further analyzed will be conducted, including tag linking, clustering of operational taxonomic units (OTUs), OTU taxonomic annotation, diversity analysis, and functional prediction. Notably, Mothur (v1.31.2) will be employed for alpha diversity analysis, while QIIME (v1.80) will be utilized for beta diversity analysis (Schloss Schloss et al., 2009; Caporaso et al., 2010). Functional prediction will be performed using PICRUSt (v2.3.0-b) (Douglas et al., 2019), and heat maps for additional visualizations will be created using the R package (v3.5.1).

#### Serum preparation and liquid chromatography coupled to tandem mass spectrometry analysis (LC–MS/MS)

2.16.2

Blood samples will be collected from the patients prior to inclusion and again 4 weeks post-treatment. The samples will be allowed to coagulate in a centrifuge tube for 30 min. After complete coagulation, the blood will be centrifuged at 1600 × *g* at low speed for 10 min at 4°C. To obtain the supernatant for LC–MS analysis, it will be transferred into a new Eppendorf tube and centrifuged for an additional 10 min at 16000 × *g*.

The separation and detection of metabolites will be performed using a Waters 2777c UPLC (Waters, USA) in conjunction with a Thermo Fisher Scientific Q Exactive HF mass spectrometer (Thermo Fisher Scientific, MA, USA). Chromatographic separation will be conducted using a Waters ACQUITY UPLC BEH C18 column (1.7 μm, 2.1 mm × 100 mm, Waters, USA), with the column temperature maintained at 45°C. In positive mode, the mobile phase will consist of 0.1% formic acid (A) and acetonitrile (B), while in negative mode, it will comprise 10 mM ammonium formate (A) and acetonitrile (B). The flow rate will be set to 0.35 mL/min, and the injection volume will be 5 μL. The Q Exactive HF (Thermo Fisher Scientific) will be utilized for primary and secondary mass spectrometry data acquisition. The full scan range will set to 70–1,050 m/z with a resolution of 120,000, and the automatic gain control target for mass spectrometry acquisitions will be set to 3e6 with a maximum ion injection time of 100 ms. The data acquisition system employed will be the Thermo Fisher Scientific Q Exactive HF, with the automatic gain control target for mass spectrometry also set to 3e6 and a maximum ion injection time of 100 ms (Dunn et al., 2011).

The BGI Metabolome Database (BMDB), mzCloud database, and ChemSpider online database will be utilized to analyze the mass spectrometry data. The results of this analysis will be compiled into a data matrix containing information such as peak areas and identification results for metabolites. The subsequent bioinformatics analysis will encompass data preprocessing, quality control, species annotation, and the identification and analysis of differences between comparison groups. Species annotation will be conducted using the Human Metabolome Database and the Kyoto Encyclopedia of Genes and Genomes (KEGG) databases. Metabolites will be functionally annotated in the KEGG PATHWAY database, focusing on biochemical metabolic and signal transduction pathways. Differences between comparison groups will be analyzed using partial least squares-discriminant analysis (PLS-DA), while a two-tailed Student’s *t*-test will be employed to determine the relative metabolite contents between groups. Metabolites with a variable importance (VIP) score >1 will considered to exhibit differential alterations between the groups.

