#### Multimodal data analysis

2.16.3

In this study, we will conduct a comprehensive multimodal data analysis by integrating fMRI metrics including ALFF, ReHo and FC, with gut microbiota alpha and beta diversity, as well as differential serum metabolite levels. To explore the associations among these variables, we will utilize Spearman correlation analysis, which is well-suited for assessing non-parametric relationships. The Bonferroni correction will be applied to adjust for multiple comparisons. Additionally, mediation analysis will be performed to validate the hypothesized “microbiota-metabolite-brain function” pathway, examining how gut microbiota may influence brain function via specific metabolites. This integrated approach aims to provide deeper insights into the complex interactions among these biological systems.

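### Declaring every metabolite with a PLS-DA VIP above 1 differential flags about one third of metabolites even when acupuncture has no effect

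*Protocol article*

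**What the plan says.** Section 2.16.2 (serum LC–MS/MS) sets out three steps in succession.

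- The model: "Differences between comparison groups will be analyzed using partial least squares-discriminant analysis (PLS-DA").
- A two-tailed t-test: this "test will be employed to determine the relative metabolite contents between groups". No significance threshold is given here; section 2.17 sets p < 0.05 for the study in general.
- The decision rule: "Metabolites with a variable importance (VIP) score >1 will considered to exhibit differential alterations between the groups".

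Section 2.16.3 (multimodal analysis) then uses the result. It correlates fMRI metrics and microbiota diversity with the selected metabolites ("as well as differential serum metabolite levels") by Spearman's method, and adds that "The Bonferroni correction will be applied to adjust for multiple comparisons". It also plans a mediation analysis "examining how gut microbiota may influence brain function via specific metabolites".

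The whole of section 2.16 is headed as mechanism exploration. The Discussion concedes that the sample is rather small for the microbiota and metabolomic work, but does not mention the selection rule.

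**The concern.** VIP measures how much a metabolite contributes to a fitted PLS-DA model relative to the other metabolites in that model. It is a ranking, scaled so that its mean square is 1, and not a measure of evidence that the groups differ. Some metabolites must therefore exceed 1 in any fit, including a fit to pure noise.

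Used as the sole criterion, VIP > 1 makes a long list of altered metabolites certain in advance. This part of the mechanistic question then cannot return a negative answer. A larger trial would not help, because the null share comes from the scaling of VIP and not from the sample size. The list is also the stated input to the correlations in section 2.16.3, so its errors travel further.

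**Working it through.** **Inputs from the protocol article.** Section 2.9: SD 1.54, difference 1.15, two-sided alpha 0.05, power 80%, 29 per group, raised to 32 for attrition. Section 2.16.2: PLS-DA with VIP > 1. The article gives no false-selection rate for this rule, so there is no stated figure to compare with. The sample size serves only as the n for the check.

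**Inputs assumed, because the article does not give them.** Components 1, 2, 3 or 5; autoscaled data; 300, 1,000 or 3,000 metabolites; four dependence structures.

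**Step 1. Sample size reproduced.** n = 2 × (1.960 + 0.842)² × (1.54 / 1.15)² = 28.15, so 29 per group; 29 × 1.10 = 31.9, so 32.

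**Step 2. Why the cut-off always selects.** With p metabolites, weights w_ja for metabolite j in component a, and SS_a the group variation explained by component a:

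VIP_j² = p × Σ_a (SS_a × w_ja²) / Σ_a SS_a

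The squared weights of each component sum to 1 over the metabolites. Hence (1/p) × Σ_j VIP_j² = Σ_a SS_a / Σ_a SS_a = 1 in every fit. VIP > 1 means only that a metabolite is above the root-mean-square importance.

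**Step 3. Null share, one component.** On autoscaled data the weight is proportional to the correlation r_j between metabolite and group, so VIP_j = |r_j| / RMS(r). With no group effect r_j is approximately normal around zero, and the share flagged is about P(|Z| > 1) = 31.7%.

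**Step 4. Null share by simulation, 29 per group.** Ranges run over 300 to 3,000 metabolites.

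| Metabolite structure | 1 component | 2 components | 5 components |
|---|---|---|---|
| Independent | 32.1–32.3% | 32.2–33.2% | 32.2–33.2% |
| Blocks, r = 0.5 | 32.3–32.5% | 32.5–37.8% | 32.5–38.6% |
| Ten common factors | 32.7–33.0% | 38.4–38.7% | 40.6–41.2% |
| Ten factors, log-normal | 34.8–35.0% | 39.3–39.4% | 39.7–40.2% |

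With 32 per group the shares lie between 32.1% and 40.9%, essentially the same. A separate run of 1,000 null data sets (29 per group, 1,000 metabolites, two components) gave a mean squared VIP of 1.000 and mean shares of 32.2% (independent) and 34.2% (blocks). No single data set fell below 29%.

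**Step 5. If the t-test were a joint condition.** In the same null data, 3.7 to 5.6% of metabolites had p < 0.05, and requiring VIP > 1 as well left those shares unchanged. Per 1,000 metabolites, that is about 50 false entries instead of about 320 to 410.

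**Step 6. What the Bonferroni step does downstream.** A null chain was simulated: 29 per group, 1,000 metabolites, two components, VIP > 1, then Spearman correlations with ten unrelated measures (the ten are an assumption), with Bonferroni over all pairs. Any false correlation appeared in about 5 to 8% of runs. The padded list does raise the bar for true links: with 320 metabolites and ten measures the threshold is 0.05 / 3,200 = 0.0000156, against 0.05 / 500 = 0.0001 for a list of 50.

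**Step 7. The remedy under the null.** Benjamini-Hochberg at 5% on the t-tests gave any false hit in about 4 to 7% of null runs, close to nominal.

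**The case against.** *The t-test may be a joint criterion.* It stands in the sentence directly before the VIP rule, concerns the same comparison, and section 2.17 supplies p < 0.05. In a condensed article this reading is plausible. It stands as an ambiguity: the text does not join the two conditions, and if they were joined the null share would fall from about one third to about 5%, still without control over the number of metabolites tested.

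*The detail may be in a full protocol or analysis plan that is not shown.* This holds for permutation tests, cross-validation and baseline adjustment, and their absence is not counted here. It does not cover a decision rule that the article does state and that does not do what it claims.

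*Bonferroni protects the conclusion.* This stands for the correlations. A reader might infer that the whole chain from microbiota through metabolites to brain function would be reported even if acupuncture did nothing. The documents do not support that: the link must still pass the correction in section 2.16.3, and under the null it does so in only about 5 to 8% of simulated runs. Bonferroni does not, however, correct the prior statement that the listed metabolites were altered.

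*The list need not reach the mediation analysis.* This also stands. Section 2.16.3 refers there only to specific metabolites and does not say how they are chosen, so the feed is a reasonable inference and no more.

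*The work is exploratory.* The abstract, the heading of section 2.16 and the Discussion say so. This lowers the priority but does not make the rule informative.

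**Conclusion.** The concern holds for the selection rule. As written, section 2.16.2 would declare about one third of metabolites altered with no treatment effect: 32 to 33% for independent metabolites, up to about 41% with correlated metabolites and several components. On the more charitable reading with the t-test, about 5% would be declared falsely. The figures rest on assumed component number, scaling, metabolite count and correlation, but the finding of roughly a third or more is stable across all settings tried, and the mean square of 1 needs no assumption about the data.

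The false statement is confined to the claim that the listed metabolites were changed by acupuncture. The list explicitly enters the correlations, where its main cost is lost power, and may enter the mediation analysis. The primary outcome, UPDRS III, and the clinical secondary outcomes are unaffected, so a reader should not infer that the trial's main result is at risk. Section 2.16.3 also speaks of mediation as validating the pathway; whether that wording is justified is a separate question and is not settled by this point. Priority: should be fixed, ideally before unblinding.

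**What to change.** In section 2.16.2, define a differential metabolite as one with a Benjamini-Hochberg q < 0.05 for the between-arm comparison. The preferred comparison is log peak area at week 4 in a linear model adjusted for the same metabolite's baseline value; Table 1 already schedules serum at both visits. Keep VIP only to rank metabolites. In section 2.16.3, carry forward only the metabolites that meet the q criterion. If VIP > 1 is retained as an additional filter, say explicitly that both conditions must be met and that the p-value is adjusted for multiplicity; that would also cure the defect.

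The change needs no new data and little extra analysis. The downside is a shorter list, possibly an empty one, which would be the right result if acupuncture does not alter serum metabolites.

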#### Multimodal data analysis

2.16.3

In this study, we will conduct a comprehensive multimodal data analysis by integrating fMRI metrics including ALFF, ReHo and FC, with gut microbiota alpha and beta diversity, as well as differential serum metabolite levels. To explore the associations among these variables, we will utilize Spearman correlation analysis, which is well-suited for assessing non-parametric relationships. The Bonferroni correction will be applied to adjust for multiple comparisons. Additionally, mediation analysis will be performed to validate the hypothesized “microbiota-metabolite-brain function” pathway, examining how gut microbiota may influence brain function via specific metabolites. This integrated approach aims to provide deeper insights into the complex interactions among these biological systems.

### Data analysis methods

2.17

Patient demographics, clinical characteristics, and gait data will be analyzed using SPSS V27.0. Measurement data will be expressed as mean ± standard deviation (mean ± SD) if they follow a normal distribution, while count data will be described using frequency and constituent ratio if they do not. For non-normally distributed data, the difference between the lower and upper quartiles (P25, P75) will be reported. Wilcoxon rank sum and Mann -Whitney U tests will be used for comparisons within and between groups. The chi-square test will be employed to analyze count data. Based on the normality of the data, either Pearson or Spearman correlation will be performed to analyze the correlations. This study will be deemed statistically significant at *p* < 0.05.

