### Randomization, allocation concealment, and blinding

2.8

Participants will be divided into two groups: the acupuncture group (receiving acupuncture treatment) and the sham acupuncture group (receiving pseudo-acupuncture treatment). The allocation ratio is set to 1:1 (*n* = 64), with randomization executed using a random group number generator in SPSS software (IBM, Armonk, NY, USA). Random numbers will be placed in opaque envelopes, which will be sealed and labeled with corresponding serial numbers to ensure confidentiality. The envelopes will be opened sequentially, and participants will be assigned to their respective treatment groups.

While patients in this trial will be blinded, it is nearly impossible to blind the practitioners and operators since they must know which acupuncture devices to use. They are prohibited from discussing the acupuncture devices or the study’s purpose with participants. Operators and assessors will be kept separate, and data analysis will be performed by an independent team. Outcome assessors and statisticians will be blinded to the treatment distribution.

To evaluate the success of blinding, patients will complete a blinding validation questionnaire (BTQ) immediately after their treatment. The BTQ consists of five questions. Blinding is considered successful if a participant completes all five questions without hesitation, reports no unusual sensations, and does not deny receiving acupuncture. Conversely, blinding is considered unsuccessful if participants identify any unusual elements of the questionnaire or deny receiving acupuncture. Otherwise, it is deemed successful.

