### Sample size estimation

2.9

The sample size was determined based on the Unified Parkinson’s Disease Rating Scale (UPDRS) III motor assessment. A previous study (Jang et al., 2020a) provided the sample size estimation. Two-sided two-sample *t-*tests with a significance level of 0.05 were employed to achieve 80% power. The analysis indicated a standard deviation of 1.54 and a mean difference of 1.15 between the two groups. Consequently, the G-Power (v3.1) sample size calculation indicated that each group will consist of 29 patients diagnosed with PIGD-subtype PD, satisfying the inclusion and exclusion criteria. However, to accommodate a 10% attrition rate, the sample size for each group was increased to 32 patients.

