### Baseline evaluation

2.14

During the baseline evaluation, the patient’s age, sex, disease duration, Hoehn–Yahr stage, UPDRS III scores, MMSE scores, MoCA scores, and levodopa equivalent dose (LED) will be assessed and recorded. To ensure the effectiveness of the study, assessments will be conducted at the same time each time the patient is in the on or off phase.

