#### Primary outcomes

2.15.1

The UPDRS III assesses a patient’s motor function by measuring various aspects, such as language, facial expressions, tremors, rigidity, limb movements, posture, and gait. A lower UPDRS III score indicates a better quality of life (Movement Disorder Society Task Force on Rating Scales for Parkinson’s Disease, 2003). This evaluation will be performed prior to inclusion, 4 weeks post- treatment, and after 8 weeks of follow-up.

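### Section 2.17 gives an independent-samples rank test to paired within-group data, and its between-group test makes no stated use of baseline UPDRS III as a covariate

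*Protocol article*

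**What the plan says.** Section 2.17 (Data analysis methods) gives one sentence on testing measurement data: "Wilcoxon rank sum and Mann -Whitney U tests will be used for comparisons within and between groups". The sentence before it concerns skewed data: "For non-normally distributed data, the difference between the lower and upper quartiles (P25, P75) will be reported". Section 2.17 names no paired test, t-test, ANCOVA or mixed model for the clinical outcomes.

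The primary outcome is a repeated measure. Section 2.15.1 says of UPDRS III: "This evaluation will be performed prior to inclusion, 4 weeks post- treatment, and after 8 weeks of follow-up". Table 1 shows UPDRS III, BBS and gait analysis at weeks 0, 4 and 12. Section 2.14 confirms that the baseline value is held for every patient: "UPDRS III scores, MMSE scores, MoCA scores, and levodopa equivalent dose (LED) will be assessed and recorded".

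Section 2.9 sizes the trial with "Two-sided two-sample" t-tests, "with a significance level of 0.05 were employed to achieve 80% power", on "a standard deviation of 1.54 and a mean difference of 1.15 between the two groups". It arrives at 29 per group, raised to 32 for attrition. Section 2.8 adds: "The allocation ratio is set to 1:1".

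**The concern.** There are two separate issues.

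**Within groups.** Wilcoxon rank-sum and Mann-Whitney U are the same procedure for two independent samples. Baseline and follow-up scores of one patient are correlated. A test that treats them as independent uses too large a variance for the difference, so its p-values are too big and real change is missed. An analyst who follows 2.17 literally would report within-group p-values that do not mean what the 0.05 threshold implies.

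**Between groups.** The named test has no place for a covariate. Baseline UPDRS III is likely to be the strongest available predictor of follow-up UPDRS III. Leaving it out of the model gives up precision in a trial planned on about 58 evaluable patients (2 × 29) and leaves chance baseline imbalance unadjusted. A rank test also does not itself estimate a difference in points, which is the scale on which the trial was sized.

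**Working it through.** **Inputs.** Difference 1.15, SD 1.54, two-sided alpha 0.05, power 80%, 29 evaluable per group (section 2.9); 1:1 allocation (section 2.8). The baseline/follow-up correlation r is not in the article, so r = 0.3 to 0.8 is assumed. The article does not say whether 1.54 is the SD of the score or of its change, so both are shown.

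**1. The plan's own figure.** Standardised difference d = 1.15/1.54 = 0.747. By the normal approximation, n = 2 × (1.54 × (1.960 + 0.842)/1.15)² = 28.15, rounded up to 29. The exact t calculation gives 29.14, with 79.8% power at 29. The stated 29 per group reproduces.

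**2. Rank-sum against signed-rank on paired data.** For two measurements with equal SD σ and correlation r, the difference has variance 2σ²(1 − r). The independent-samples test works as if it were 2σ², which is too large whenever r > 0. Simulation with 29 bivariate normal pairs, 4,000 to 6,000 runs:

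| r | Type I error, rank-sum | Type I error, signed-rank | Power for 0.5 SD change, rank-sum | Power for 0.5 SD change, signed-rank |
|---|---|---|---|---|
| 0.3 | 2.1% | 4.3% | 44% | about 58% |
| 0.5 | 0.7% | 5.1% | 42–43% | 71% |
| 0.7 | 0.1% | 4.5% | 42% | 91% |
| 0.8 | below 0.1% | 4.5% | 40–41% | 98% |

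The loss depends on the size of the change. For a within-group shift of 0.747 SD, rank-sum power is 82%, 86%, 91% and 94% over the same r. Signed-rank power is 90%, 97%, above 99% and about 100%.

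**3. Between groups, 1.54 taken as the SD of the score.** ANCOVA residual SD = 1.54 × √(1 − r²). At r = 0.5 this is 1.54 × 0.866 = 1.33; at r = 0.7 it is 1.54 × 0.714 = 1.10. Power at 29 per arm:

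| r | Mann-Whitney on follow-up score | ANCOVA |
|---|---|---|
| 0.3 | 76–78% | 82–83% |
| 0.5 | 76–78% | 89–90% |
| 0.7 | 76–78% | 97% |
| 0.8 | 76–78% | 99.4–99.6% |

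Mann-Whitney on change scores, under the same reading of 1.54, gives about 61–63%, 77–79%, 93–94% and 99%. That is below ANCOVA at each r, with almost no gap at 0.8.

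**4. Between groups, 1.54 taken as the SD of change.** ANCOVA SD = 1.54 × √((1 + r)/2), a variance reduction of (1 − r)/2: 25% at r = 0.5, 15% at 0.7, 10% at 0.8. ANCOVA power at 29 per arm is 90%, 86% and 84%. Unadjusted power on change is 79.8% by t-test and about 78% by Mann-Whitney.

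**5. Cost of the rank test itself.** Under normality its efficiency relative to the t-test is 3/π = 0.955. The 29 patients act like 29 × 0.955 = 27.7, giving about 78% power instead of 79.8%.

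**The case against.** The case on the other side has force on several points.

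- *A naming slip.* Two tests and two kinds of comparison are listed in the same order, so signed-rank was probably meant for the within-group part. That is plausible, but the text names a different test and must be corrected.
- *Conservative and off the main contrast.* This stands. The wrong paired test produces no excess of false positives. A reader might infer that the primary randomised comparison is invalid; nothing in the article supports that, because an unadjusted between-group test is valid under randomisation.
- *Baseline may be used after all.* A reader might infer that the trial ignores its baseline data. The article does not say whether follow-up or change scores are compared, and a Mann-Whitney test on change would use the baseline. Nor can it be said that most of the precision is lost. The variance saving is r² against the follow-up score (25% at 0.5, 49% at 0.7) and (1 − r)/2 against change, which stays below one half for any positive r.
- *t-test in 2.9, rank test in 2.17.* A reader might infer a contradiction. The test sentence follows one about non-normal data and may cover only such data. Means and SDs are planned for normal data, so a parametric branch is implied though its test is not named. The power cost is also only about 2 points.
- *Left to the SAP.* Covariate adjustment commonly is, so its absence is no error and it is offered here as an improvement. The same argument does not excuse the within-group test, which 2.17 states affirmatively and wrongly.

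**Conclusion.** The point holds in two parts of different weight.

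First, 2.17 names a test that is wrong for paired within-group comparisons of UPDRS III, BBS and gait. With 29 pairs and r between 0.3 and 0.8, it runs at a type I error of about 2% down to about 0%, and it has about 40–44% power for a 0.5 SD change where signed-rank has 58–98%. This is a stated error that needs correcting, but it is conservative and does not reach the treatment comparison.

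Second, the between-group test is valid but inefficient. Adjusting for baseline would raise power from 76–78% to about 82–99.6% (r from 0.3 to 0.8) if 1.54 is the score SD, or from 78–80% to about 84–90% (r from 0.8 to 0.5) if it is the change SD. Which range applies cannot be settled from the article, because neither r nor the meaning of 1.54 is given. All figures assume bivariate normal scores with equal SDs and 29 evaluable patients per arm.

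**What to change.** In section 2.17:

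1. Name the Wilcoxon signed-rank test or the paired t-test for within-group change, and label those results descriptive, not evidence of efficacy.
2. Analyse UPDRS III between groups by ANCOVA, or a mixed model over the follow-up visits, with baseline UPDRS III as covariate. Report the adjusted mean difference with its 95% confidence interval. Treat BBS and each gait parameter the same way, each with its own baseline.
3. Keep the Mann-Whitney test as a sensitivity analysis, stating whether it is applied to follow-up or change scores.

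This puts the primary result on the mean-difference scale used for the sample size in section 2.9. No new data are needed, since every baseline value is already scheduled. The costs are a small amendment to an ethics-approved, registered protocol, and reliance on a linear model, which the rank-based sensitivity analysis helps to check.
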